## Discussion

### Importance of the project

Unemployment is a significant problem in the UK, with disabled people being more likely to be unemployed than those without a disability. The most recent labour force national statistics indicate that 45.6% of disabled people aged 16–64 was in employment in 2011, compared to 76.2% of working age adults without a disability. Those with a disability are also more likely to work fewer hours than those without a disability with around a third (33.8%) of disabled adults working part time hours [17].

Mental health problems such as depression are common in those with physical health problems and those who are unemployed [2]. cCBT interventions may help to improve mood, coupled with employment and health-specific modules, this intervention may improve mood as well as job-seeking and employment potential.

We hope that recruiting from Remploy will identify people who might otherwise fail to engage in traditional NHS-based services thus addressing the wider treatment gap. The design allows a detailed description of those recruited, in order to understand the age, current and past treatments, severity and chronicity of depression among those recruited.

If this study shows that the trial design is feasible, then this will lead to a larger, funded RCT of the intervention which may have important implications for supporting disabled people who are seeking to gain employment.

### Determining the feasibility of the study design

As outlined in the aims sections, the feasibility of the trial design will be determined by considering four main factors: recruitment, adherence, acceptability and follow-up rates. In the future RCT, the recruitment period is estimated to be 6 months, with the aim of recruiting approximately 100 people in total. Therefore, an acceptable recruitment rate in the current feasibility study is 3–4 participants per week for 6 months.

The adherence rate is defined as the number of online modules completed. We have examined completion rates of equivalent modules delivered in face to face classes. In our pilot study 65% of people attended half of face to face sessions [7]. We judge an acceptable completion rate as 55% of people completing four or more of the eight course modules. The number of support sessions participants take part in will also be used as an indicator of engagement and will provide information regarding the feasibility of the caseloaders taking on this role.

As discussed in the “Methods/design” section, we will be using the Client Satisfaction Questionnaire to assess acceptability of the intervention. Scores on this measure range from 8–32 with a median of 20. For this study scores ≥20 will be considered as acceptable.

Finally, in relation to the feasibility of collecting data, the main outcomes relating to employment are collected by Remploy as part of their standard procedures, so we expect to have approximately 100% follow-up rate for these variables (number of applications, employment status etc.) The remaining data concerning mood will be collected by the researcher. From our knowledge and experience of online trials, we believe a follow-up rate of ≥70% is acceptable for secondary outcomes; therefore, this follow-up rate would indicate feasibility of data collection.

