### Research questions

Primary question:Is the study design feasible—is it possible to recruit from Remploy, randomise participants and collect data at baseline, 3 months and 6 months?

Secondary questionsb.To what extent will participants adhere to the intervention?b.Is the Living Life package satisfactory/acceptable to participants?c.How many participants will be needed for a sufficiently powered future RCT? (Efficacy data at 3 and 6 months will be used for the future sample size estimation).

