### Participants

The aim is to recruit 100 participants in total for this feasibility study, 50 intervention participants and 50 control participants to allow for comparison at the 3-month follow-up point and 6-month exit point. We will recruit males and females aged 16 +.

*Inclusion criteria:* Participants will be willing to take up the offer of LL and appropriate for usual Remploy support—and with no active risk to self at initial Remploy assessment (this is not routinely investigated, but if suicidality is disclosed at the initial assessment, the individual will not enter the study). Individuals must be able to register on the website, read and understand the LL resources via the internet or DVD; at home or in the Remploy office.

*Exclusion criteria:* Individuals will be excluded if they are unwilling or unable to use the LL approach and/or if they are at active risk of suicide, identified in which case usual care (referral to GP) will occur as is normal Remploy practice.

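### The recruitment criterion is derived from a future trial of about 100 people whose size this study is meant to determine, and its lower limit delivers only 78 of that 100

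*Protocol article*

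**What the plan says.** Under Determining the feasibility of the study design, the Protocol article gives the premise first: "In the future RCT, the recruitment period is estimated to be 6 months, with the aim of recruiting approximately 100 people in total". The next sentence draws the criterion from it: "Therefore, an acceptable recruitment rate in the current feasibility study is 3–4 participants per week for 6 months".

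Other sections bear on that premise:

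- Research questions, secondary question c, is "How many participants will be needed for a sufficiently powered future RCT". The answer is to come from this study's efficacy data at 3 and 6 months.
- The abstract's Discussion and the last sentence of Statistical analyses also say that the future trial's sample size will follow from this study, the latter by a power calculation at the end.
- Participants sets the present study's own target: "The aim is to recruit 100 participants in total for this feasibility study, 50 intervention participants and 50 control participants".
- Importance of the project describes the trial that would follow a positive result as larger. The section on collaboration with Remploy calls it large.

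Recruitment belongs to the primary research question and is the first of the four factors by which feasibility will be determined.

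**The concern.** There are two linked difficulties.

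First, the criterion assumes a size for the future RCT that the article elsewhere treats as unknown. That size also equals the target of the feasibility study, although the RCT is expected to be bigger. A recruitment rate judged against it has no established link to the trial it is supposed to support.

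Second, the criterion is presented as a consequence of recruiting about 100 in 6 months, yet its lower end does not deliver 100 in 6 months.

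What is at stake is the answer to the primary question. Recruitment could be reported as acceptable when the study has fallen well short of its own target, and that result could be carried into a funding case for a trial whose required rate was never compared with it.

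**Working it through.** **Inputs.** Target: about 100 (Determining the feasibility of the study design, there attributed to the future RCT; Participants gives the same number for the present study). Period: 6 months. Acceptable rate: 3–4 per week. The conversion of 6 months to 26 weeks is mine; 24 and 25 weeks are shown as variants.

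**Step 1: reproduce the stated range.** Required rate = target / weeks = 100 / 26 = 3.85 per week. This lies inside 3–4, so the range reproduces as a whole-number bracket.

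**Step 2: what each end delivers.** Total = rate × weeks.

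| Weeks taken as 6 months | Rate needed for 100 | Total at 3 per week | Total at 4 per week |
|---|---|---|---|
| 26 | 3.85 | 78 | 104 |
| 25 | 4.00 | 75 | 100 |
| 24 | 4.17 | 72 | 96 |

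At 26 weeks the lower end falls short by (100 − 78) / 100 = 22%. The midpoint of 3.5 per week gives 91. At 3 per week, reaching 100 takes 100 / 3 = 33.3 weeks, about 7.7 months. A shorter conversion makes the shortfall larger.

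**Step 3: compare the statements about the future RCT.**

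- The feasibility section puts it at about 100.
- The abstract, question c and Statistical analyses leave it to be determined.
- The Discussion expects it to be larger than this study.
- Participants sets this study at 100.

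A trial of about 100 is not larger than one of 100, and a size still to be calculated cannot be a fixed input. These statements cannot all stand.

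**Step 4: illustration only.** The article gives no effect size, standard deviation or power for the future RCT, so its true required rate cannot be computed. To show how far it could vary, assume two-sided alpha 0.05, 80% power, equal arms and a simple comparison of means: n per arm = 2 × (1.96 + 0.8416)² / d² = 15.70 / d², rounded up. The last two columns divide the total by 0.70, the article's minimum follow-up rate for mood data.

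| Assumed d | Total, complete data | Per week over 26 weeks | Total, 70% follow-up | Per week over 26 weeks |
|---|---|---|---|---|
| 0.6 | 88 | 3.4 | 126 | 4.8 |
| 0.5 | 126 | 4.8 | 180 | 6.9 |
| 0.4 | 198 | 7.6 | 283 | 10.9 |
| 0.3 | 350 | 13.5 | 500 | 19.2 |

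The required rate could lie within 3–4 per week or several times above it. Nothing in the article chooses between these rows.

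**The case against.** **The range is not an arithmetic error.** A reader might infer from 3 × 26 = 78 that the figure is simply wrong. It is not: 3.85 lies inside 3–4, the upper end gives 104, and the target is itself approximate. This objection stands, and the point is confined to the lower limit.

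**A lower acceptable rate may be deliberate.** The same section sets its adherence criterion at 55%, below the 65% seen in its pilot, so a threshold below the reference value has a precedent. A tolerance of this kind would be legitimate. But the adherence threshold is presented as a judgement, whereas the recruitment range is presented as following from 100 in 6 months. Nowhere is 78 named as enough, so a clarifying statement is still needed.

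**The reference to the future RCT may be a slip.** The present study also targets 100, and the sentence reads naturally if that was meant. This is plausible, but the text does not say so. If it is right, the sentence needs correcting and the contradiction disappears; the lower-limit point remains.

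**The study need not be accepting too slow a rate for the RCT.** A reader might infer that 3–4 per week is only a fraction of what a powered trial would need. The document does not support that. The effect sizes above are assumptions, and at d = 0.6 with complete data 88 participants, or 3.4 per week, would do. The 70% applies to mood data; employment outcomes are expected to be followed up almost completely. The simple formula ignores the baseline measurement and covariates in the planned mixed model. Nor is the RCT tied to the two offices named under Trial status, and more offices would raise the total weekly rate. All of this stands, so the table shows only that the required rate is open.

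**Conclusion.** The concern holds in a limited form. The recruitment criterion rests on a size for the future RCT that the article contradicts in several places. Its lower limit, taken over 26 weeks, allows 78 participants, 22% below the 100 from which it is derived. The stated range does bracket the required 3.85 per week, so there is no calculation error in the range as a whole.

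The 22% depends only on converting 6 months to 26 weeks. The contradiction depends on no assumption: it is between statements in the same document, and it is not a matter of detail left to an analysis plan. No conclusion is drawn about the size the future RCT will need. This should be changed because the criterion decides part of the primary question, but it does not threaten the design or the conduct of the study.

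**What to change.** 1. State which trial the figure of about 100 refers to. If it is the present study, correct the sentence accordingly.
2. Align the lower limit with the target: 100 in 26 weeks, about 3.85 per week. Alternatively, keep 3 per week and state explicitly that about 78 participants is the accepted minimum, with the reason.
3. Remove the fixed size for the future RCT. Judge its recruitment feasibility by comparing the observed rate per office per week, with its confidence interval, against N / (planned offices × planned weeks), where N is the answer to question c.

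The cost is a few sentences, with no change to design or data collection beyond recording enrolment by office. The one real price is a stricter criterion if the first option in item 2 is taken: moving the floor from 78 to 100 raises it by 22 / 78 = 28%.

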### Follow-up data collection

The main follow-up point will be at 3 months with an additional follow-up assessment at 6 months. The data will be used to:Determine the proportion of people taking up the LL intervention, adherence to the intervention and follow-up rates.Describe the difference in proportion of people in work at 12 weeks between the LL group and the TAU control group or if not in work the number of interviews attended and job submissions made (measuring motivation).Describe the subsequent number (frequency) and total (days) off work over 3 months and 6 months in both arms comparing within group comparisons from baseline, and between-groups at 3 and 6 months.Describe and compare impact on mood, social function and satisfaction at 3 months and 6 months in both arms comparing within group comparisons from baseline, and between-groups at 3 and 6 months. This data will be used for the future sample size calculation.

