### Statistical analyses

Baseline characteristics will be summarised for all participants as well as for the IA and DAC groups separately. Participant uptake and adherence to the online intervention, defined as the number of online sessions completed and the number of support sessions participants took part in, as well as data follow-up rates, will be summarised and presented as percentages.

To assess efficacy, repeated measures analysis will be carried out using an intention to treat approach by means of a linear mixed effects model with the time (baseline, 3 months, 6 months) and group (control, intervention) main effects and their interaction as fixed effects, and participant as a random effect. Models will be adjusted for age, gender and antidepressant use at baseline. Tukey post-hoc comparisons will be carried out with a familywise error rate of 5%. These models will be used to estimate and test the statistical significance of the within-group differences between time points and the between-group differences at each time point. Finally, a power calculation will be carried out to determine the required sample size for a future RCT.

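### Employment is labelled the main outcome, yet the sample-size sentence sits with mood, and two of the three employment comparisons (job search among those not in work, time off work from baseline) are unsound as written

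*Protocol article*

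**What the plan says.** All references are to the protocol article.

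- **Ranking of outcomes.** Determining the feasibility of the study design says that "the main outcomes relating to employment are collected by Remploy as part of their standard procedures", with follow-up expected to be close to 100%. It then turns to the mood data collected by the researcher and says "we believe a follow-up rate of ≥70% is acceptable for secondary outcomes". The abstract says the future trial is to address both mood and employment status.
- **Employment comparisons.** Follow-up data collection lists three. The first is the difference between the arms in the proportion in work at 12 weeks. The second continues the same sentence: "or if not in work the number of interviews attended and job submissions made (measuring motivation". The third is "Describe the subsequent number (frequency) and total (days) off work over 3 months and 6 months in both arms comparing within group comparisons from baseline", and also between groups.
- **Sample size.** In the same section, the item on mood, social function and satisfaction ends "This data will be used for the future sample size calculation". Research questions refers only to efficacy data at 3 and 6 months, and Statistical analyses names no outcome for the power calculation.
- **Model.** Statistical analyses assesses efficacy "by means of a linear mixed effects model with the time (baseline, 3 months, 6 months) and group (control, intervention) main effects", with their interaction, a participant random effect, and adjustment for age, gender and baseline antidepressant use. It does not name the outcome.
- **Population.** Benefits to participants describes adults who are out of work. The Remploy section says that referrals usually are.

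**The concern.** Three things do not fit together.

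First, the outcomes called main are not the ones beside which the sample-size sentence stands, and the one model specified does not fit a yes/no status that is nearly constant at entry. Sizing the future trial is a stated research question, so the outcome used for it matters.

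Second, being in work at 12 weeks is a consequence of treatment. If the package helps the more active job seekers into work, they leave the not-in-work group faster in the immediate-access arm. Those who remain are less active on average, so a package that works can appear to lower motivation, which is what the counts are said to measure.

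Third, time off work can arise only in someone who has gained a job. It is therefore also confined to a group formed after randomisation, and people without a job have no earlier value from which to measure a within-group change.

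**Working it through.** **The plan's own figure.** The only sample size is 100 (50 per arm), with no effect size, SD, event rate or power. It can be checked only against the recruitment target: 3 × 26 = 78 and 4 × 26 = 104 over six months, and 100/26 = 3.85 per week. The figures agree. No stated number is wrong.

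**Which comparisons keep the randomised groups?**

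| Comparison | Who is counted | Baseline used | Sound? |
|---|---|---|---|
| In work at 12 weeks | Whole arms | None | Yes |
| Interviews, job submissions | Only those not in work | None | No: subset formed after randomisation |
| Number and days off work | In effect, only those who gain work | Within-group change | No: same subset problem, and no meaningful baseline |

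If time off work were instead read as time without a job, everyone out of work at entry would start at the ceiling and could change in one direction only. The within-group comparison would still be uninformative.

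**Size of the subset bias (all inputs assumed).** Let motivation m be standard normal and job submissions be 10 + 3m + 3e, with e standard normal and no treatment effect on submissions. The SD is 3√2 = 4.24. People enter work when a latent score that correlates ρ with m exceeds a threshold, so that a proportion p enters work. Among those not in work, the mean of m is −ρ·φ(z)/(1−p), where z is the (1−p) normal quantile. The spurious deficit in SD units is (ρ/√2) times the difference between arms in φ(z)/(1−p).

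- 20% v 30% in work: 0.280/0.8 = 0.350 and 0.348/0.7 = 0.497; the difference is 0.147. Dividing by √2 gives 0.104, so the deficit is 0.05 SD at ρ = 0.5 and 0.10 SD at ρ = 1.
- 10% v 20%: 0.05 to 0.11 SD.
- 20% v 35%, and 30% v 45%: 0.08 to 0.16 SD.

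A simulation of 2,000,000 people under the same model gave the same values. The direction is always against the arm that gets more people into work.

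**Future sample size (assumed inputs; 80% power, two-sided 5%, 1:1).**

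Mood, n per arm = 2(1.96 + 0.8416)²/d²:

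| Standardised difference d | Per arm | Total | Total after 30% loss |
|---|---|---|---|
| 0.3 | 175 | 350 | 350/0.7 = 500 |
| 0.4 | 99 | 198 | 283 |
| 0.5 | 63 | 126 | 180 |
| 0.6 | 44 | 88 | 126 |

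The 30% loss corresponds to the 70% follow-up that the protocol accepts for mood.

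Employment, n per arm = [1.96√(2p̄(1−p̄)) + 0.8416√(p₁(1−p₁) + p₂(1−p₂))]²/(p₁−p₂)², with follow-up taken as complete. For 20% v 30%: (1.200 + 0.512)²/0.01 = 293.2, so 294 per arm.

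| In work | Per arm | Total | Power at 50 per arm | 95% CI half-width at 50 per arm |
|---|---|---|---|---|
| 10% v 20% | 199 | 398 | 29% | 14 points |
| 15% v 25% | 250 | 500 | 24% | 16 points |
| 20% v 30% | 294 | 588 | 21% | 17 points |
| 20% v 35% | 138 | 276 | 39% | 17 points |
| 30% v 40% | 356 | 712 | 18% | 19 points |
| 30% v 45% | 163 | 326 | 34% | 19 points |

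The ranges overlap: a mood difference of 0.3 SD needs 350 before loss, more than the 276 for 20% v 35%. The feasibility section already foresees about 100 people in the future trial. That is below every employment total here, and near the lower end of the mood totals.

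**The case against.** The best defence is that this is a feasibility study. Its primary question is whether people can be recruited, randomised and followed, and the follow-up list mostly says it will describe. No primary conclusion depends on the ranking of employment and mood, and that ranking comes from a Discussion paragraph about follow-up rates. All of this stands, and it limits the consequence to the efficacy summaries and the design of the next trial. But calling a comparison descriptive does not remove its bias.

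The absence of a method for proportions or counts may be left to an analysis plan that is not shown. That also stands, and the absence is not part of this point.

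It may also be said that applications appear to be recorded for everyone, and that the work-or-else wording could be meant as a tiered description. If so, the sound analysis is already within reach, but the text as written restricts the counts to those not in work.

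Four stronger readings are tempting and not supported:

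- *That every employment comparison is unsound.* The proportion in work at 12 weeks uses whole arms and no baseline.
- *That the mixed model is declared to be for mood only, or will be fitted to work status.* The outcome is not named. That it is meant for the scores is an inference from its form.
- *That the future trial will be sized on mood and underpowered for employment.* The sample-size sentence follows the mood item, but Research questions and Statistical analyses leave the outcome open.
- *That a baseline for time off work cannot exist.* Referrals are only usually out of work, and Baseline data collection includes employment information. The supportable statement is that it has no meaningful value for people out of work.

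**Conclusion.** The point holds in limited form. The label of main outcome and the placing of the sample-size sentence conflict and need to be reconciled. The job-search comparison, followed as written, is biased against a package that gets people into work. The bias is about 0.05 to 0.16 SD if 10 to 30% of controls and 10 to 15 percentage points more in the other arm find work, and if motivation drives both job submissions and finding work (ρ from 0.5 to 1). The direction follows from that last assumption; the size rests on all of them. The baseline comparison of time off work is not interpretable for the population described.

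On sample size, the assumed inputs give 276 to 712 in total for employment and 88 to 350 for mood (126 to 500 after 30% loss). The choice of outcome can change the answer several-fold, but the documents do not settle which is larger. The primary feasibility conclusion does not change.

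**What to change.** 1. State which outcome is intended as primary for the future trial, and align the main and secondary labels with it.
2. Report the difference in proportion in work at 3 months in all randomised participants, with a 95% CI.
3. Analyse interviews and submissions over 0 to 3 months in all randomised regardless of work status, or as an ordered outcome with being in work as the top category. The ordered form is easier to interpret, because people who find work stop searching and a lower total count need not mean lower motivation.
4. Replace number and days off work by days in paid work since randomisation, in all randomised, compared between arms with no baseline comparison.
5. Compute the future sample size for both employment and PHQ-9, show the range of inputs, and let the declared primary outcome govern.

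The cost is rewording and a little more analysis. Employment status and applications are already collected routinely by Remploy; that its records also hold interview counts and job start dates is an assumption to confirm. The future sample size may come out larger.
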